### Randomization

Randomization will occur in blocks of four to ensure approximately equal numbers in each arm. Participants will be asked to read the study information and give their consent online. They will then be directed to create a password-protected account to login to the OWC. After login, participants will be randomized into two groups. The intervention group will have immediate access to The Toolbox, whereas the control group will be allocated to the wait-list for 4 weeks.

### Statistical Analysis

The primary analysis is based on intention to treat, and missing values from all randomized participants will be imputed with 50 samples redrawn from the original data. The primary outcome will be assessed using random effects mixed modeling, with the well-being score as the dependent variable. The independent variables are time, group, and the time × group interaction (product) term, which are clustered over age, gender, geographical location, work status, cultural background, education level, and living circumstances to account for possible correlated readings. Sensitivity analyses and secondary continuous outcomes will be assessed similarly, but also adjusted for potential confounders. All results will be reported with 95% CI and *p* values. A *p* value < 0.05 (two tailed) was taken to be significant. All analyses will be performed using Stata version 13.1 (College Station, TX, USA) [46].

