### Study Design

This is a standard parallel arm clinical trial comparing the effectiveness and cost effectiveness of control and intervention arms offered over 4 weeks. Group 1 represents the intervention arm (OWC with The Toolbox) and Group 2 represents the waitlist control arm (OWC without The Toolbox). In this study, participants in the intervention arm will be able to access the active component of the trial, The Toolbox, through the OWC straight away. Participants in the control group will gain access to The Toolbox after 4 weeks. Once participants follow the online links as described in the recruitment section, they will be directed to the project’s landing page (Figure 1). Once there, they will be required to complete the steps outlined in Figure 4.

All participants will receive regular SMS and email prompts from the OWC to remind them to complete study measures. As detailed in Table 1, assessments will be administered at sign up, and at 4 weeks. In addition, participants will be prompted to regularly monitor their mood, energy and sleep.

**Table 1 table1:** Assessment scales administered at each time point during the study.

Instrument	Measurement	Baseline	After 4 Wk
Mental Health Continuum Short Form	Well-being/Positive mental health	X	X
Center for Epidemiologic Studies Depression Scale	Symptoms of depression	X	X
Assessment of Quality of Life-four dimensions index	Quality of life data	X	X
Resource use questionnaire	Cost effectiveness		X
Demographics	Date of birth, gender, postcode, employment, education, cultural background, and living conditions	X	
Heuristic well-being questions	Feelings, energy, and sleep	Weekly	Weekly

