### Sample Size

The primary outcome measure is change in well-being as measured by MHC-SF. A total of 180 completed participants (90/arm) are required to provide 80% power to detect a difference of 0.37 in improvement between arms with a two-tailed type 1 error of 0.05. This assumes an overall standard deviation of 0.63 at baseline and 0.81 at 1-month follow-up as found in Bolier et al [16], and a conservative correlation of 0 between baseline and follow-up scores. Considering the higher attrition level found by Bolier et al [16] (37.8%) this study will aim to recruit a sample of 250 participants.

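### The primary time × group model is valid but does not adjust for the baseline MHC-SF already collected, which gives up precision by an amount that depends on an unstated 4-week correlation

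*Protocol article*

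**What the plan says.** The Statistical Analysis section of the protocol article fixes the primary model: "The primary outcome will be assessed using random effects mixed modeling, with the well-being score as the dependent variable". It then gives the terms: "The independent variables are time, group, and the time × group interaction (product) term". Baseline MHC-SF is therefore one of the two outcome readings, not a covariate, and no common baseline mean is imposed on the arms. The variables over which the terms are said to be clustered are demographic and social. Further adjustment is confined to other analyses: "Sensitivity analyses and secondary continuous outcomes will be assessed similarly, but also adjusted for potential confounders". Baseline MHC-SF is not named there either.

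Under Study Design, "assessments will be administered at sign up, and at 4 weeks", so the MHC-SF has two time points. The Sample Size section works on the same contrast: "The primary outcome measure is change in well-being as measured by MHC-SF". It assumes "a conservative correlation of 0 between baseline and follow-up scores". All randomised participants enter the analysis, because "missing values from all randomized participants will be imputed with 50 samples redrawn from the original data".

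**The concern.** With two time points, the time × group term is the difference between arms in mean change. Randomisation makes the true baseline means equal. The free group term therefore estimates a quantity known to be zero, and its sampling error passes into the treatment estimate. The change contrast subtracts the baseline with a fixed weight of 1. Adjustment uses the weight the data support, which is the slope of week 4 on baseline. Both target the same effect, so precision is given up with no reduction in bias in return.

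Power is at stake in a trial that expects heavy attrition. The article states the model terms outright, so this is a choice it has made and not a detail left to an analysis plan.

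**Working it through.** **Inputs.** From Sample Size: difference 0.37, SD s0 = 0.63 at baseline and s1 = 0.81 at follow-up, correlation r = 0, two-sided 5% level, 80% power, 90 completers per arm, 250 recruited, 37.8% attrition. From Primary Outcome Measure: MHC-SF test-retest reliability of .68 over 3-month periods and .65 over 9 months. Powers below use the normal approximation, Φ(0.37/SE − 1.96).

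**The protocol's own figure.** At r = 0 the SD of change is √(0.63² + 0.81²) = √1.0530 = 1.026. The number per arm is 2 × 1.0530 × (1.960 + 0.842)² / 0.37² = 121. The protocol states "A total of 180 completed participants (90/arm) are required", which these inputs do not reproduce; 90 per arm gives 67.7% power. That is a separate matter and is needed here only as background.

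**What the model estimates.** On simulated complete two-wave data (r = 0.3, 90 per arm), the mixed-model interaction was 0.3005 with SE 0.1247. The simple difference in mean change gave the same two values. ANCOVA on the same data had SE 0.1144.

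**Variance per participant, complete data.**
- Change: s0² + s1² − 2r·s0·s1
- Adjusted: s1²(1 − r²)
- Gap: (s0 − r·s1)², which is never negative and is zero at r = 0.63/0.81 = 0.78

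At r = 0 the gap is 0.63² = 0.3969, and 0.3969/1.0530 = 38%. With 90 per arm, SE = √(2 × variance/90):

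| r | SD change | SD adjusted | Variance cut | Power, change | Power, adjusted |
|---|---|---|---|---|---|
| 0 | 1.026 | 0.810 | 38% | 67.7% | 86.5% |
| 0.3 | 0.864 | 0.773 | 20% | 81.9% | 89.5% |
| 0.5 | 0.737 | 0.701 | 9% | 92.1% | 94.3% |
| 0.65 | 0.624 | 0.616 | 3% | 97.8% | 98.1% |
| 0.68 | 0.599 | 0.594 | 2% | 98.5% | 98.7% |
| 0.78 | 0.509 | 0.509 | 0% | 99.8% | 99.8% |
| 0.9 | 0.367 | 0.353 | 7% | >99.9% | >99.9% |

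The gain does not fall steadily with r: it reaches zero near 0.78 and then rises again.

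**With attrition.** 250 × (1 − 0.378) = 155.5 completers, or 77.75 per arm out of 125 randomised. The planned analysis uses every baseline, so its per-arm variance is s1²(1 − r²)/77.75 + (s0 − r·s1)²/125. The adjusted estimate has s1²(1 − r²)/77.75. This assumes dropout unrelated to outcome and a covariance that is free to differ between the two times.

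At r = 0, the planned SE is √(2 × (0.6561/77.75 + 0.3969/125)) = 0.152 and the adjusted SE is √(2 × 0.6561/77.75) = 0.130.

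| r | Power, planned | Power, adjusted |
|---|---|---|
| 0 | 68.0% | 81.3% |
| 0.3 | 79.3% | 84.7% |
| 0.5 | 89.0% | 90.8% |
| 0.65 | 96.0% | 96.3% |

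**The case against.** The planned contrast is the one the protocol says it wants. It defines the outcome as change, powers a difference in improvement, and estimates that without bias. This stands: nothing in the analysis section is false or contradictory.

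The protocol also offers r = 0 as a conservative bound and not as an expectation. The only MHC-SF correlations it gives are .65 and .68. At 0.68 the slope is 0.68 × 0.81/0.63 = 0.87, so subtracting the baseline outright is nearly optimal and adjustment gains 2–3% of the variance. This also stands, with two limits. Those values cover 3 and 9 months, and no 4-week value is given for this population. The small gain also depends on the unequal SDs: with equal SDs the variance ratio is (1 + r)/2, a cut of 16% at r = 0.68.

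Three stronger readings are tempting, and the documents do not support them:
- That the choice of contrast is what takes the trial below 80% power. The shortfall at r = 0 comes mainly from the Sample Size section, where 90 per arm does not follow from the inputs and 250 recruits leave about 155 completers. At 121 completers per arm the planned contrast would have 80%.
- That attrition takes the planned analysis down to 61% at r = 0. That is a complete-case figure for 77.75 per arm. The protocol analyses all randomised participants, which gives about 68%.
- That the planned contrast ignores chance baseline imbalance. It subtracts the imbalance in full; what it lacks is the best weight.

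**Conclusion.** The point holds as a loss of efficiency of uncertain size. It is neither a bias nor an error of validity. The planned interaction is asymptotically never more precise than the baseline-adjusted estimate. Adjustment removes 38% of the variance at the protocol's planning value of r = 0, 9% at r = 0.5, and 2–3% at the reliability values the protocol cites. Allowing for attrition, the difference in power runs from about 13 percentage points at r = 0 to 0.3 points at r = 0.65.

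These figures rest on the two stated SDs, the normal approximation and dropout unrelated to outcome. The 4-week correlation, which decides the size, is not in the document. Since r is unknown, the contrast that protects power at low r and costs almost nothing at high r is the better primary choice.

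**What to change.** In the Statistical Analysis section, state that the primary estimate is the week-4 difference in MHC-SF between arms, adjusted for baseline MHC-SF. Either of two forms will do:
- a mixed model with time and time × group, a common baseline mean for both arms, and a covariance between the two readings at participant level; or
- ANCOVA of week-4 MHC-SF on arm and baseline MHC-SF, run within the planned imputation.

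Keep the difference in mean change as a supportive analysis.

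The cost is one sentence. No new data or participants are needed, and all randomised participants stay in the analysis. The downside is negligible: in a single dataset the adjusted SE can be trivially larger, as in one simulated set at r = 0.68 (0.0948 against 0.0941). The sample size needs its own correction, which this change does not replace.

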### Primary Outcome Measure

The primary outcome is mental health (well-being), assessed using the MHC-SF [37]. This scale consists of 14 questions measuring three areas of well-being, namely, emotional, psychological, and social. The tool diagnoses mental health as flourishing, moderately mentally healthy, and languishing, consistent with the Complete State Model of Health theory. The MHC-SF has been validated with adolescents and adults in the United States, South Africa, and the Netherlands. It has an internal consistency over Cronbach alpha = .80 [38-41]. The test-retest reliability of the MHC-SF over three successive 3-month periods averaged .68, and the 9-month test-retest reliability was .65 [40]. A clinically significant change will be defined as a change in diagnostic outcome (languishing, moderately mentally healthy, and flourishing) between measures before and after the intervention in at least one of the well-being categories (emotional, psychological, and social). We will also consider changes in heuristic trackers as reflective of behavioral change (sleep, mood, energy).

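### The primary mixed model assigns correlated readings to seven demographic variables and never names the participant; followed as written, the standard error of the time-by-group test is wrong

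*Protocol article*

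**What the plan says.** The Statistical Analysis section of the protocol article states: "The primary outcome will be assessed using random effects mixed modeling, with the well-being score as the dependent variable". It goes on: "The independent variables are time, group, and the time × group interaction (product) term", and then adds of these terms: "which are clustered over age, gender, geographical location, work status, cultural background, education level, and living circumstances to account for possible correlated readings". No random effect or clustering level for the participant is named for this model anywhere in the article. The next step is described separately: "Sensitivity analyses and secondary continuous outcomes will be assessed similarly, but also adjusted for potential confounders".

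Three other places bear on the point. Under Study Design, "assessments will be administered at sign up, and at 4 weeks", so each person contributes two MHC-SF scores. Under Randomization, people are allocated individually: "Randomization will occur in blocks of four to ensure approximately equal numbers in each arm". Under Primary Outcome Measure, the scale's scores are reported to be stable within a person: the average over 3-month periods is .68, and "the 9-month test-retest reliability was .65".

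**The concern.** In an individually randomized trial with two visits, the dependence that matters is between a person's own two scores. Sharing a gender, work status or education level does not make two people repeated measurements of one unit, and a two-level variable can hardly support a variance component. The sentence is more than a detail left out. It says what the clustering is for and lists the variables that are to do it, and the participant is not on the list. Nor does the list read easily as loosely worded covariate adjustment, because adjustment for confounders is introduced afterwards as something additional.

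The time-by-group term is the trial's primary test, and the secondary continuous outcomes are to be modelled in the same way. A wrong standard error would carry into every confidence interval and p value from these models.

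**Working it through.** **Inputs, all from the protocol article**
- SDs 0.63 at baseline and 0.81 at one month; difference in improvement 0.37; two-sided 5%; 90 completers per arm (Sample Size).
- Within-person correlation r: 0 assumed for sample size (Sample Size); .65 to .68 reported as test-retest reliability (Primary Outcome Measure).
- Two readings per person (Study Design, Table 1).

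**The plan's own figure.** The Sample Size section states: "A total of 180 completed participants (90/arm) are required to provide 80% power". At r = 0 the variance of a change score is 0.63² + 0.81² = 0.3969 + 0.6561 = 1.053. The number per arm is 2 × 1.053 × (1.960 + 0.842)² / 0.37² = 121, and power at 90 per arm is 67.7%. The stated 90 per arm is therefore not reproduced; it would need r of about 0.26. That is a separate matter. Here 90 per arm serves only as the planned number analysed.

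**Standard error of time-by-group with n per arm, complete pairs**
- Participant as the level: √[2(s0² + s1² − 2·r·s0·s1)/n].
- No participant term, demographics unrelated to the score: √[2(s0² + s1²)/n].

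At r = 0.65 the true change variance is 1.053 − 2 × 0.65 × 0.63 × 0.81 = 1.053 − 0.663 = 0.390.
- True SE: √(2 × 0.390/90) = 0.093.
- SE without a participant term: √(2 × 1.053/90) = 0.153.
- Ratio: √(1.053/0.390) = 1.64.
- Actual type I error: 2 × [1 − Φ(1.96 × 1.644)] = 0.0013.
- Power without a participant term: Φ[(0.37 − 1.96 × 0.153)/0.093] = 77.5%.
- Power with it: Φ(0.37/0.093 − 1.96) = 97.8%.

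| r | SE, participant level | SE, no participant term | Ratio | Type I error, no participant term | Power, no participant term | Power, participant level |
|---|---|---|---|---|---|---|
| 0 | 0.153 | 0.153 | 1.00 | 0.050 | 67.7% | 67.7% |
| 0.5 | 0.110 | 0.153 | 1.39 | 0.006 | 73.9% | 92.1% |
| 0.65 | 0.093 | 0.153 | 1.64 | 0.0013 | 77.5% | 97.8% |
| 0.68 | 0.089 | 0.153 | 1.71 | 0.0008 | 78.4% | 98.5% |

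**Check of different implementations by simulation.** There were 180 participants with two readings each and r = 0.65; the true SE is 0.093. The numbers of categories (age 10, gender 2, location 3, the others 4 each) and demographics unrelated to the score are assumptions.

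| Implementation | Mean model SE |
|---|---|
| Crossed random effects for the seven demographics | 0.147 |
| Random intercept for participant | 0.093 |
| Cluster-robust on participant | 0.093 |
| Cluster-robust on gender (2 clusters) | 0.073 |
| Cluster-robust on age (10 clusters) | 0.089 |
| Cluster-robust on joint cells of all seven | 0.093 |

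The crossed model was fitted to only 8 simulated data sets and the participant intercept to 40; the cluster-robust rows used 400. The joint cells come out right because they number about 179 for 180 people, so they nearly identify the individual.

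**The case against.** The strongest reply is that random effects modelling of two visits ordinarily carries a participant intercept, that a condensed article may leave it unsaid, and that the demographic clause is a garbled account of further terms. This is possible, and it means the documents do not establish that the analysis will lack a participant term. It does not rescue the sentence, which attributes the correlated readings to the demographics. An analyst following it would have no instruction to include the participant.

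A second reply is that the sample size calculation assumes r = 0, where the two standard errors coincide. The article itself calls that value conservative, uses it only for sample size, and reports .65 to .68 elsewhere.

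A third reply is that the direction of the error is not fixed, and this stands. A reader might infer that the test is bound to be conservative and run at about 0.1%. That follows only if the demographics are random effects and the participant is absent. Cluster-robust errors on gender err the other way, on age they are nearly right, and joint cells give almost the correct value, although the text does not describe joint cells.

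A reader might also put power at about 68%. That figure arises at 78 per arm, that is, 250 × (1 − 0.378) = 155.5 completers, and so mixes in a separate attrition shortfall. At the planned 90 per arm the figure is about 78%.

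**Conclusion.** The stated rule puts the correlation in the wrong place and should be corrected. If it is followed literally, the standard error of the primary test is wrong. With demographic random effects and no participant term, it is up to about 1.64 times too large at r = 0.65: type I error is about 0.001, and power at 90 per arm is about 78% instead of about 98%. With cluster-robust errors on a variable with few levels, it tends to be too small, which would make the test too liberal.

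These sizes rest on four assumptions: the reported 3- to 9-month reliability carries over to 4 weeks; the cited SDs apply; pairs are complete, so the planned imputation is not reflected; and the demographics do not predict the score. To the extent that they do predict it, they absorb part of the within-person correlation and the inflation shrinks. What is certain is the misdirected wording; the size and sign of the error are conditional on how it is implemented.

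**What to change.** In the Statistical Analysis section, name the participant as the random-effect (clustering) level for the two MHC-SF scores, or specify an unstructured within-participant covariance for the two visits. Delete the clause that uses the seven demographic variables to handle correlated readings. The same wording then serves the secondary continuous outcomes.

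If adjustment for the demographics is wanted, they can enter as fixed covariates. That, like constraining the baseline means to be equal across arms, is an optional choice and not part of this correction.

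The cost is one sentence. It needs no new data and no change of software.

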### Cost-Effectiveness Analysis

An economic evaluation will be conducted alongside the trial to estimate the relative cost effectiveness of The Toolbox compared with the wait-list. The evaluation will take the form of a cost-effectiveness analysis based on a primary outcome of cost per unique visit to the OWC. Utility-based outcomes will also be incorporated into the analysis allowing a secondary outcome to be cost per quality-adjusted life year (QALY) gained (based on the AQOL-4D values) [47].

The cost and outcome data will be estimated for every participant within the trial. Costs will be estimated by combining data on resource use associated with both the intervention and control groups with unit costs for each of the resource items. Resource use data will be collected using the resource use questionnaire described earlier. Unit costs (eg, staff wages or opportunity cost of time lost from work, school, or household activities) will be collected from published data sets including those from the Australian Bureau of Statistics and the Australian Government Fair Work Ombudsman. A participant-level analysis will be undertaken to determine the mean costs, increases in number of visits to the OWC, and QALYs for each trial arm. To test the robustness of the economic evaluation results, nonparametric bootstrapping and appropriate sensitivity analyses will be carried out and results will be reported in terms of incremental cost-effectiveness ratios and cost-effectiveness acceptability curves. The final results will be presented in the CONSORT format for reporting randomized trials [48] and the CONSORT-EHEALTH extension [49].

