Another novel feature of this study resides in the fact that the intervention is not limited to a clinical population. This opens up opportunities to explore a number of variables that could be highly significant for future interventions; for example “Does well-being improve in the absence or presence of pathology?” and “What are the most effective mechanisms to recruit young people from different backgrounds and engage them with activities to improve their well-being?”

Finally, it is expected that the health economic analysis that will be conducted will determine whether improving well-being in the target population is associated with lower health care costs.

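### The lead economic ratio, cost per OWC visit, contains no health term and uses an effect count that is structurally likely to favour the Toolbox arm

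*Protocol article*

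**What the plan says.** The Cost-Effectiveness Analysis section of the protocol article sets out "to estimate the relative cost effectiveness of The Toolbox compared with the wait-list", in the form of "a cost-effectiveness analysis based on a primary outcome of cost per unique visit to the OWC". The Abstract repeats this choice. Cost per QALY, from the AQOL-4D, is named as a secondary outcome. The same section later describes the effect side of the participant-level analysis as "increases in number of visits to the OWC", with results reported as incremental ratios and acceptability curves.

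Under Study Design, both arms have the OWC and they differ in The Toolbox. Intervention participants "will be able to access the active component of the trial, The Toolbox, through the OWC straight away". For the other arm, "Participants in the control group will gain access to The Toolbox after 4 weeks". Some reasons to visit are shared: "All participants will receive regular SMS and email prompts from the OWC to remind them to complete study measures", and Table 1 schedules weekly well-being questions.

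The trial's primary outcome is the MHC-SF (Primary Outcome Measure), which is the effect unit in neither economic ratio. The Abstract's Conclusions anticipate that, if the intervention is effective, this type of intervention will be a valid and cost-effective support to mental health treatment. Principal Findings expects the economic work to "determine whether improving well-being in the target population is associated with lower health care costs".

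**The concern.** An incremental cost-effectiveness ratio is informative when its denominator is a benefit that the comparison could either produce or fail to produce. Here the denominator is use of the platform that houses the active component, and one arm has an additional reason to use it. More visits in the Toolbox arm would show that the offer was taken up. They would not show that anyone was better off.

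At stake is the reading of the lead economic result. A low cost per extra visit could stand as the primary cost-effectiveness finding next to a null MHC-SF difference. The ratios that could reveal the lack of benefit would be secondary (cost per QALY) or not planned at all (cost per unit of MHC-SF).

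**Working it through.** The article gives no visit count, cost per participant or value per visit, so there is no stated figure to reproduce. The check is of what the ratio contains.

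**Step 1: the ratio.** With C for mean cost and V for mean OWC visits per participant (1 = Toolbox arm, 0 = wait-list arm):

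lead ratio = (C1 − C0) / (V1 − V0)

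Neither MHC-SF nor AQOL-4D appears in it. Its value is the same whether the MHC-SF difference is large, zero or negative.

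**Step 2: what feeds V in each arm during the 4 weeks (Study Design, Table 1).**

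| Reason to visit the OWC | Toolbox arm | Wait-list arm |
|---|---|---|
| Prompts to complete study measures | yes | yes |
| Weekly mood, energy and sleep questions | yes | yes |
| Reaching The Toolbox | yes | no, until after 4 weeks |

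The first two rows are common to both arms. The third is present in one arm only, and it is the treatment itself. So V1 − V0 is partly a measure of exposure to the assigned treatment and is likely to be positive. Nothing in the article fixes its size.

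**Step 3: illustration with assumed inputs.** Suppose The Toolbox has no effect on MHC-SF or quality of life. Take an extra cost of AUD 5, 20 or 50 per participant and 0.5 to 8 extra visits. All of these are assumptions, since the documents supply none. Cost per extra visit (AUD) = extra cost / extra visits:

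| Extra cost | 0.5 visits | 1 | 2 | 4 | 8 |
|---|---|---|---|---|---|
| 5 | 10.00 | 5.00 | 2.50 | 1.25 | 0.625 |
| 20 | 40.00 | 20.00 | 10.00 | 5.00 | 2.50 |
| 50 | 100.00 | 50.00 | 25.00 | 12.50 | 6.25 |

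In each row the ratio improves 16-fold (8 / 0.5) as visits rise, with no health gain in any cell. A ratio on MHC-SF or QALYs would instead show added cost for zero gain. The table shows how the measure behaves. It is not a forecast for this trial.

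**Step 4: the ratio against the conclusions.** The Abstract speaks of cost-effective support for mental health. That needs a health effect in the denominator. Principal Findings asks about well-being and health care costs. That needs well-being and costs examined together. A cost per visit supplies neither.

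**The case against.** The strongest reply is that engagement is worth measuring here. Online Recruitment and Engagement reports high attrition in internet interventions and links higher use to better well-being, and Principal Findings expects the design to improve engagement. Use is voluntary, so extra visits would be a genuine behavioural response to the offer. Cost per QALY is planned, MHC-SF remains the trial's primary outcome, and a null result on either would be reported beside the visit ratio. The cost-effectiveness statement in the Abstract is conditional on the intervention proving effective.

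Much of this stands. It justifies reporting visits, and it means that the clinical result is not at risk. It does not justify making visits the lead effect in a cost-effectiveness ratio. A link between use and well-being in other studies is not evidence that extra visits in this trial bring a gain, and the trial measures the gain directly.

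Three stronger readings are tempting, and the documents do not support them.

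- A reader might infer that allocation itself produces the visit difference because each Toolbox session adds a visit. The article says only that The Toolbox is reached through the OWC. A session can fall within a visit made for the weekly questions, and time in a recommended app need not involve the OWC.
- A reader might take a unique visit as one per person, which would leave no difference between arms and no defined ratio. The same section speaks of "increases in number of visits to the OWC", which points away from that reading. What remains is that two terms are used where one would do.
- A reader might object that an acceptability curve on visits has no accepted value scale. The article gives no value for a unit of MHC-SF either, so this does not separate the two measures.

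**Conclusion.** The point holds as a weakness in the choice of lead economic measure. Cost per OWC visit has no health term, and its denominator is partly exposure to the assigned treatment. It is structurally likely to favour the Toolbox arm and could look favourable with no MHC-SF gain, so it cannot by itself carry the article's economic conclusions. The planned cost per QALY softens this without removing it. It ranks second, the Abstract draws the secondary outcomes from a subsample, and Limitations says that completion of secondary measures is not assured.

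The size is unknown. The conclusion rests on the access route in Study Design and on the form of the ratio, not on any assumed visit count. A favourable visit ratio is possible, not certain: visits may hardly differ, and time spent on the OWC may itself be costed. The primary clinical analysis is untouched, so this is a worthwhile and inexpensive improvement rather than a flaw that threatens the trial.

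**What to change.** In Cost-Effectiveness Analysis and in the Abstract:

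1. Make cost per unit gain in MHC-SF the lead cost-effectiveness ratio. It is the trial's primary outcome, and Table 1 already schedules it at baseline and 4 weeks.
2. Keep cost per QALY from the AQOL-4D as the cost-utility result.
3. Report OWC visits by arm descriptively, as engagement, and use one term for a visit throughout.

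The cost is a change of labels and one further ratio. No new data are needed. The downside is that the MHC-SF ratio will probably be less precise than one based on visits. Two limits remain. Subsidiary Outcome Measures takes resource use from a sample of 50 participants at the end of the trial, which constrains every ratio, including the one proposed. And a cost per unit of MHC-SF does not on its own settle whether better well-being goes with lower health care costs, although it does bring cost and well-being into the same analysis.
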